### Primary outcome measure

#### *Psychological distress*

Distress will be measured using the Depression Anxiety and Stress Scales (DASS-21) short version [40]. The DASS-21 is a set of three self-report scales designed to measure the negative emotional states of depression, anxiety and stress as well as total distress [40]. Each of the three DASS-21 scales contains 7 items. The depression scale measures dysphoria, hopelessness, devaluation of life, self-deprecation, lack of interest/involvement, anhedonia and inertia. The anxiety scale measures autonomic arousal, skeletal muscle effects, situational anxiety, and subjective experience of anxious affect. The stress scale assesses difficulty relaxing, nervous arousal, being irritable and impatient. The total score is the sum of these three subscale scores. Participants are asked to rate the extent to which they have experienced each state over the past week, using a 4-point severity/frequency scale. The DASS-21 scales have good concurrent validity with the Beck measures of depression and anxiety (BDI & BAI) and good internal consistency and reliability [40].

### Secondary outcome measures

#### *The prostate cancer-related quality of life scales (PCa-QoL)*

The impact of erectile dysfunction on sexual and masculine identity will be measured using the PCa-QoL [41], which measures men’s perceptions of early prostate cancer treatment outcomes, focussing on behavioural, interpersonal and emotional changes that patients attribute to prostate cancer [41]. The scale contains 84 Likert type items that fall into 11 scales including: 1. Urinary control (behavioural and interpersonal implications of impaired control of one’s bladder); 2. Sexual ability - sexual intimacy (ability to perform sexually and feelings of frustration, embarrassment or failure); 3. Sexual confidence (confidence and anxiety about intimate activity and sexual thoughts); 4. Spouse affection (misgivings about demonstrations of affection with one’s spouse), 5. Masculine self-esteem; 6. Health worry (uncertainty about one’s health); 7. PSA concern; 8. Cancer control; 9. Informed decision; 10. Regret; and, 11. Positive outlook.

#### *International index of erectile function (IIEF)*

The IIEF [42] is a 15-item self-report measure that was developed to assess sexual function among men with Erectile Dysfunction (ED) [42]. The IIEF instructs respondents to answer items according to functioning during the past 4 weeks. Responses to items are summed to determine the total IIEF score (range 5–75). Rosen et al. [42] reported high internal consistency, for the total IIEF scale (α = 0.91), as well as high test-retest reliability (*r* = 0.82).

#### *Kansas marital satisfaction scale (KMS)*

The KMS [43] is a common measure of relationship satisfaction. It is a 3-item self-reported questionnaire measuring general relationship satisfaction. Final scores on the KMS range from 3 to 21 with higher scores indicating higher relationship satisfaction. A recent meta-analysis of 398 articles evaluated the reliability of seven different relationship satisfaction measures using Cronbach’s alpha estimates [44]. The authors found the KMS to be the strongest overall measure based on reliability alone with an average of *r* = .95 across studies.

#### *Communication patterns questionnaire-short form (CPQ-SF)*

The CPQ-SF [45,46] is an 11-item self-report questionnaire that measures communication within intimate relationships. The CPQ-SF asks respondents to identify typical communication styles when either issues or problems arise and during discussion of issues or problems. Respondents are asked to rate the likelihood that certain issues/problems occur on a 9-point scale from very unlikely to very likely.

#### *Dyadic sexual communication scale (DSC)*

The DSC [47] was originally developed as a 13-item scale to measure a respondent’s self-reported perception of their communication with their partner related to sexual relationships. Subsequently, Choi, Catania, and Dolcini [48] created a 4-item version of the DSC scale. The short-form DSC has 4 items requesting ratings on a 5-point scale: strongly disagree, disagree, neutral, agree, and strongly agree. Reliability of the 4 item version of the DSC was found to be acceptable taken from a male sample as part of the larger study mentioned above (Cronbach’s alpha = .65) [48].

#### *General confidence*

Because of the strong link between sexual potency and general confidence, a 1-item scale was created to assess general confidence (*I feel confident in most areas of my life*) which will be rated a 5-point scale: *almost never/never* to *almost always/always*.

#### *Healthcare service utilisation and demographics*

Participants will also be asked to record the number of contacts they have with additional support services including psychiatrists, psychologists and social workers as well as attending a support group or accessing support from the cancer council or other online resources. Degree of engagement of the participant’s partner in the program and completion of the exercises will also be assessed post-intervention.

Demographic details include age, date of birth, marital status, employment status, gross annual income, ethnicity, languages spoken. Other participant details including postcode, prostate cancer date of diagnosis, date of treatment, type of treatment, use of oral erectile function medications (e.g. use of Viagra or cialis), use of injection therapies for erectile function (e.g. Caverject injections), and use of other mechanical aids for erectile function will also be collected.

#### *Program and forum satisfaction questionnaires*

Program completion will be tracked and recorded through the online system which will allow reporting of the proportion of the program completed by each user as well as details about which modules are most accessed. A questionnaire has been developed for this study for the purpose of measuring the level of program satisfaction and level of inclusion of partners. Respondents will be presented with open-ended questions relating to the “best” and “worst” parts of the program and how the program could be improved, including any additional features they might find useful. If men do not work through all the modules they will be asked for reasons. An equivalent questionnaire has been developed to measure satisfaction with the moderated forum.

### Participants

A medium effect size is estimated for the primary outcome measure, total distress, as measured by the DASS-21 total score between groups across the five assessment points. To power the study at the 80% level, based on an alpha level of .05 with an estimated medium effect size (f = .25) and with three groups completing five assessment points, 125 complete responses will be required. To account for an estimated 20% drop-out rate a total of 150 participants will be required; 50 per group.

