**Methods/design:**

This study utilises a RCT design with three groups receiving: 1) the 6-module My Road Ahead intervention alone; 2) the My Road Ahead intervention plus a moderated online forum; and 3) the moderated online forum alone. It is expected that 150 men with localised prostate cancer will be recruited into the RCT. Online measures will assess men’s psychological distress as well as sexual and relationship adjustment at baseline, post-intervention, 3 month follow-up and 6 month follow-up. The study is being conducted in Australia and participants will be recruited from April 2012 to Feb 2014. The primary aim of this study is to evaluate the efficacy of My Road Ahead in reducing psychological distress.

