### Procedure

Participant consent will be obtained using an online consent process. The consent form is provided to the participant in PDF format. Participants are asked to confirm that they understand the study conditions, that they have received a copy of the participant information and that they consent to take part in the study by selecting three check-boxes during the consent process. Participants will then move on to create a personal, password protected account on the My Road Ahead website and complete the baseline questionnaires. After completing the baseline questionnaires participants will then be randomly assigned using a computer generated sequential 1-to1- to 1 allocation across the three (3) groups. Participants and researchers involved in the management of the project are not blinded to the randomisation outcomes. Group 1 participants will receive access to My Road Ahead, the 6 module online program. Group 2 participants will get access to My Road Ahead plus access to the moderated forum. Group 3 participants will receive access to the moderated forum only.

Participants in all groups will receive a weekly email reminder to return to the program and/or forum and to encourage them to continue to participate in the research over the course of the 10 weeks of the intervention phase. Participants will also receive three reminder emails to complete the questionnaires at each time point.

Participants in all groups will undertake the online assessment at five time points; baseline, week 5, post-intervention (week 10 for group 3) and 12 weeks post intervention (week 22 for group 3), and 6 months post-intervention (see Figure 1).

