### Statistical analyses

Data will be analysed using repeated measures Multivariate Analysis of Variance (MANOVA) with between and within subjects factors examined while controlling for age. To examine any bias that may arise as a consequence of attrition, baseline data will be examined to explore if there are any statistically significant factors associated with participants who drop out compared to those who do not. This will allow an analysis for attrition bias in the final results based on the predicted probability of attrition as recommended by Rubin [49] and Heckman [50]. An intention to treat analysis and then longitudinal hierarchical linear model analyses will be performed [51,52], avoiding the need for the imputation of missing data.

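### The drop-out allowance is miscalculated: 150 randomised with 20% drop-out leaves 120 completers, not the 125 the plan says it needs for 80% power

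*Protocol article*

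**What the plan says.** The sample size is set in the Participants section of the protocol article. The aim is given as "To power the study at the 80% level", with alpha .05 and a medium effect of f = .25 on the DASS-21 total score. On that basis, "with three groups completing five assessment points, 125 complete responses will be required". The next sentence turns this into a recruitment target: "To account for an estimated 20% drop-out rate a total of 150 participants will be required; 50 per group".

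The Abstract (Methods/design) repeats the target: "It is expected that 150 men with localised prostate cancer will be recruited into the RCT". The Procedure section describes a "computer generated sequential 1-to1- to 1 allocation across the three (3) groups", which agrees with 50 per group. No other allowance for attrition appears in the article.

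**The concern.** Three numbers are fixed in two adjacent sentences: completers needed (125), drop-out (20%) and men randomised (150). Any two of them determine the third, and the third given does not follow. The allowance seems to have been added as 20% of the completers instead of being taken as 20% of those randomised.

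What is at stake is the power claim for the primary outcome. If the trial recruits exactly as planned and loses exactly the proportion it expects to lose, it ends with fewer complete cases than it says it needs.

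**Working it through.** **Inputs, all from the Participants section unless noted**

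- Alpha 0.05, power 80%, f = 0.25
- Groups k = 3, assessments m = 5
- Completers required: 125
- Drop-out: 20%
- Randomised: 150, 50 per group
- Allocation 1:1:1 (Procedure)
- Main analysis: repeated-measures MANOVA (Statistical analyses)

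**Step 1. Reproduce the 150.**

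- Multiplying: 125 × (1 + 0.20) = 150 exactly. This is evidently the form used.
- Dividing, the correct form: 125 / (1 − 0.20) = 156.25, rounded up to 157. For three equal groups the next multiple of three is 159 (53 per group).

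**Step 2. What 150 delivers.**

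- 150 × 0.80 = 120 completers, or 40 per group.
- Shortfall: 125 − 120 = 5, which is 4% of the requirement.
- Largest drop-out that still leaves 125: 1 − 125/150 = 16.7%.
- Check of the corrected targets: 157 × 0.80 = 125.6 and 159 × 0.80 = 127.2, both above 125.

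**Step 3. Reproduce the 125.** The article does not name the test behind this figure. A group-by-time test in a repeated-measures MANOVA (Pillai trace) matches the stated inputs and the planned analysis. For that test:

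- s = min(k − 1, m − 1) = min(2, 4) = 2
- df1 = (k − 1)(m − 1) = 8
- df2 = s(N − k − (m − 1) + s) = 2(N − 5)
- noncentrality λ = N × s × f² = N × 2 × 0.0625

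| N | df2 | λ | Power |
|---|---|---|---|
| 120 | 230 | 15.0 | 0.783 |
| 124 | 238 | 15.5 | 0.7995 |
| 125 | 240 | 15.625 | 0.8035 |

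The smallest N with at least 80% power is 125, exactly the plan's figure. The 125 is therefore sound under this reading and has no slack: one man fewer falls just below 80%. At 120 power is 78.3%, which is 1.7 points under the stated 80% and about 2 points under the value at 125.

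**Step 4. Sensitivity to the choice of test.** The wording could also describe a between-groups test averaged over the five assessments, with λ = N × f² × m / (1 + (m − 1)ρ), df1 = 2 and df2 = N − 3. The within-person correlation ρ is not stated, so it is varied here as an assumption.

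| ρ (assumed) | N for 80% | Power at 120 |
|---|---|---|
| 0.50 | 96 | 0.888 |
| 0.70 | 121 | 0.799 |
| 0.72 | 123 | 0.790 |
| 0.73 | 124 | 0.786 |
| 0.74 | 126 | 0.782 |
| 0.75 | 127 | 0.777 |

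This test calls for about 125 men only when ρ is near 0.72 to 0.74, and there power at 120 is 0.78 to 0.79. Both readings that lead to a requirement of about 125 therefore fall slightly under 80% at 120.

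**The case against.** The strongest reply is that the slip hardly matters. It costs about two points of power, biases no estimate and leaves the type I error untouched. The 20% is an unreferenced estimate and f = .25 is a generic medium effect, so a modest error in either could move power as much. This stands as a comment on size. It does not make the three numbers consistent.

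A second reply is that the Statistical analyses section also plans an intention-to-treat analysis and hierarchical linear models without imputation. Such models use men with partial follow-up, so the 30 expected drop-outs would not all be lost to the analysis. This too is partly right, and the practical loss may be smaller than a complete-case calculation shows. How much smaller depends on when men leave, which is not stated. The requirement is nevertheless expressed in complete responses, the MANOVA is listed first and in its usual form uses complete cases, and no calculation in the article credits partial data.

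A third reply is that the 78.3% rests on a test the article does not name. That is fair, and any restated power should name its test. The shortfall in completers needs no such assumption.

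**Conclusion.** The concern holds. The required completers, the drop-out rate and the number randomised cannot all be true. At the plan's own drop-out the trial ends five completers short, and the stated 80% power is not supported. That conclusion is arithmetic on the plan's own figures.

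The consequence is small: power of about 78% instead of 80%, assuming that the 125 came from the MANOVA group-by-time test and that only complete cases count. The design is not invalidated. The paragraph is wrong as written and should be corrected, because it supports the power claim for the primary outcome.

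**What to change.** Restate the Participants paragraph in one of two ways.

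1. **Keep 150 and correct the claim.** Suggested text: *With 150 men randomised and 20% drop-out, 120 completers (40 per group) are expected, giving about 78% power for the group-by-time test in a repeated-measures MANOVA (f = .25, alpha .05); 125 completers, and 80% power, are reached only if drop-out is 16.7% or less.* The sponsor should confirm that this is the test behind the 125. The cost is one corrected sentence and a slightly less favourable power figure, with no extra participants.
2. **Keep 80% power at 20% drop-out and correct the target.** Randomise 157 men, or 159 (53 per group) for equal groups, and change the 150 in the Abstract to match. The cost is seven or nine more men.

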### Statistical analyses

Data will be analysed using repeated measures Multivariate Analysis of Variance (MANOVA) with between and within subjects factors examined while controlling for age. To examine any bias that may arise as a consequence of attrition, baseline data will be examined to explore if there are any statistically significant factors associated with participants who drop out compared to those who do not. This will allow an analysis for attrition bias in the final results based on the predicted probability of attrition as recommended by Rubin [49] and Heckman [50]. An intention to treat analysis and then longitudinal hierarchical linear model analyses will be performed [51,52], avoiding the need for the imputation of missing data.

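### The first-named analysis, a repeated-measures MANOVA, is a completers analysis without imputation, and the plan does not say whether it or the hierarchical linear model decides the DASS-21 hypotheses

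*Protocol article*

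**What the plan says.** In the protocol article, the Statistical analyses section makes three statements, in this order.

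- The model: "Data will be analysed using repeated measures Multivariate Analysis of Variance (MANOVA) with between and within subjects factors examined while controlling for age".
- Attrition: baseline data of men who drop out are compared with those of men who stay, and "This will allow an analysis for attrition bias in the final results based on the predicted probability of attrition".
- Intention to treat: "An intention to treat analysis and then longitudinal hierarchical linear model analyses will be performed", with the stated benefit of "avoiding the need for the imputation of missing data".

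The Participants section sizes the trial on complete data: "with three groups completing five assessment points, 125 complete responses will be required". It then adds an allowance: "To account for an estimated 20% drop-out rate a total of 150 participants will be required; 50 per group".

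The Aims and hypotheses section makes DASS-21 total the primary outcome, with two hypotheses. H1 compares the two My Road Ahead arms with forum only. H2 compares My Road Ahead plus forum with My Road Ahead only. Neither section says which of the named analyses tests them.

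**The concern.** A repeated-measures MANOVA works on each man's full vector of outcomes. If nothing is imputed, one missed questionnaire out of five removes him altogether, including the assessments he did complete. A man who answers up to the 3-month follow-up but not at 6 months contributes nothing, although the hypotheses also concern the earlier time points.

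The analysis set then depends on who stays in follow-up. Under the Procedure section, participants and the researchers managing the project know the allocation, and the programme is self-directed. Loss related to arm or to distress is therefore plausible, and comparing only completers no longer compares the groups as randomised.

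The second issue is precedence. The MANOVA and the hierarchical model use different sets of men and make different assumptions about missing data. If they disagree on DASS-21 total, the plan gives no rule for which one stands, and the choice could be made after both are seen.

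**Working it through.** **Inputs.** From Participants: 80% power, alpha .05, f = .25, three groups, five assessments, 125 complete responses, 20% estimated drop-out, 150 in total. From Procedure: 1:1:1 allocation; baseline plus four later assessments.

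**Step 1: reproduce the 125.** For a MANOVA group-by-time test (Pillai trace) with k = 3 groups and five times:
- time contrasts p = 5 − 1 = 4; group contrasts q = 3 − 1 = 2; s = min(p, q) = 2
- df1 = p × q = 8
- df2 = s(N − k − p + s) = 2(N − 5)
- noncentrality λ = s × N × f² = 2 × N × 0.0625 = 0.125N

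| N | df2 | λ | Power |
|---|---|---|---|
| 124 | 238 | 15.5 | .7995 |
| 125 | 240 | 15.625 | .8035 |

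So 125 is the smallest N reaching 80%, an exact match to the stated figure.

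**Step 2: is the match unique?** Other candidates were tried.
- Other MANOVA noncentrality conventions give 128 or 129.
- A one-way ANOVA gives 158.
- A within-between repeated-measures ANOVA gives 27 at a correlation of .5.
- The between-groups test of a repeated-measures ANOVA gives 96 at a correlation of .5, 121 at .7 and 127 at .75. A correlation between the last two could also give 125, but the document states none.

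The MANOVA group-by-time test gives 125 from the stated inputs alone and is the method named in the analysis section. This is good evidence, not proof, that the trial was sized on it.

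**Step 3: what the MANOVA would hold at the stated drop-out.** Excluded: 150 × 0.20 = 30. Analysed: 150 × 0.80 = 120. With N = 120, df2 = 230 and λ = 15.0, power is .783, against .803 at 125. With all 150 complete it would be .884.

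The 120 falls below 125 because 150 is 125 × 1.2, whereas 125 / (1 − 0.2) = 156.25, that is 157.

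**Step 4: scattered missed assessments (assumption; the document gives no rate per visit).** If each of the four later assessments is missed independently:
- 5% each: 0.95⁴ = 0.815, and 150 × 0.815 ≈ 122 complete men, power .791
- 10% each: 0.90⁴ = 0.656, and 150 × 0.656 ≈ 98 complete men, power .674

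**Step 5: set the statements side by side.** There are two ways to read the closing sentence.
- *Intention to treat comes before the hierarchical model*, as the wording of the sequence suggests. The only other model named is the MANOVA, and without imputation it cannot include all randomised men.
- *The hierarchical model is the intention-to-treat analysis.* This can work without imputation, because the model uses whatever assessments each man supplied. The first-named and apparently powered analysis is still completers-only, and precedence is still unstated.

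The problem remains on either reading.

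**The case against.** The strongest reply is that the protocol never calls the MANOVA primary and never calls it the intention-to-treat analysis. Intention to treat stands in a separate sentence beside the hierarchical models and the remark on imputation, so the natural reading is that those models deliver it. Sizing a trial with a simpler complete-data formula does not make that formula the primary analysis. All of this stands: the MANOVA's lead is an inference from word order and the sample-size match. A reader might infer that the plan mislabels a completers analysis as intention to treat, or that it lacks a suitable method. The document supports neither.

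It may also be said that attrition is already addressed. The planned analysis based on predicted probability of attrition may help to diagnose or adjust for bias. It does not bring the excluded men back into the MANOVA.

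On size, 20% is an estimate and not a minimum, and a fall in power from 80.3% to 78.3% is small. It is tempting to attach a bias to the loss, for example by supposing that drop-outs in one arm improve less. Nothing in the document gives such a difference, and similar loss in every arm would largely cancel in the contrasts.

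Finally, a journal article condenses, and model detail such as covariance structure belongs in a fuller document. That is accepted and not held against the plan. What remains is the article's own text: two analyses of one outcome with no order between them, the first of which cannot meet the promise made later in the paragraph.

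**Conclusion.** The concern holds in a limited form. The first-named analysis, to which the sample size appears to be tied, is a completers analysis unless data are imputed, and the paragraph says imputation is avoided. At the estimated 20% drop-out it would leave out about 30 of 150 randomised men and have power of about 78%. Under the assumed missed-visit rates of 5% and 10%, power is about 79% and 67%. These powers rest on the Pillai group-by-time calculation above, with no adjustment for age.

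The more serious consequence is not the lost power. The analysis that decides H1 and H2 is undetermined, and the one named first does not keep all randomised men. The direction and size of any resulting bias cannot be derived from the document.

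**What to change.** In Statistical analyses:

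- Name the hierarchical linear (mixed) model as the single primary analysis of DASS-21 total. Include all randomised men in their allocated arm with all available assessments, and test H1 and H2 as contrasts within that model.
- State that this model assumes data are missing at random. It is not protected if men leave because of later distress that was never recorded.
- Present the analysis based on predicted probability of attrition as a sensitivity check on that assumption.
- Keep the repeated-measures MANOVA, if at all, as a labelled completers sensitivity analysis.

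The cost is a few sentences. The hierarchical model and the attrition analysis are already planned, so no new data are needed.

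### The stated MANOVA treats baseline DASS-21 as one of five repeated outcomes and names only age as a covariate, so it tests change from baseline, which is valid but less precise than baseline adjustment

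*Protocol article*

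**What the plan says.** In the protocol article, Statistical analyses names a repeated measures MANOVA first, "with between and within subjects factors examined while controlling for age". Age is the only covariate named. The same section then announces an intention-to-treat analysis and hierarchical linear models. It does not say how the baseline score enters those models, or which of the two approaches is primary.

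Three other statements fix the role of baseline in the MANOVA:

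- Procedure: "Participants in all groups will undertake the online assessment at five time points; baseline, week 5, post-intervention", followed by the two later follow-ups. Baseline is the first of the five.
- Procedure: "After completing the baseline questionnaires participants will then be randomly assigned". The baseline score is therefore a pre-randomisation measurement that every randomised man has.
- Participants: the effect assumed for the sample size is on the "DASS-21 total score between groups across the five assessment points", and "with three groups completing five assessment points, 125 complete responses will be required".

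The hypotheses under Aims and hypotheses concern greater reductions in distress from before to after the intervention and at the 3 and 6 month follow-ups.

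**The concern.** When baseline is a level of the within-subject factor, the group-by-time interaction compares arms on change from baseline. A change score subtracts the whole baseline value, which amounts to a regression slope of 1. With equal variances the slope that minimises the variance is rho, so for any rho below 1 the change score over-corrects and carries extra noise. Using baseline as a covariate, or a longitudinal model with one common baseline mean, estimates the same treatment difference with smaller variance.

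What is at stake is precision on the primary outcome, in a trial with 50 men per arm. The measurement needed is already collected from everyone before allocation. Adjusting for age does not replace it.

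**Working it through.** **Inputs from the protocol article.** Three groups, five assessments including baseline, alpha .05, power 80%, f = .25, 125 complete responses, 150 randomised, 20% drop-out. The article gives no standard deviation and no correlation between assessments, so rho below is an assumption shown over a range.

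**Step 1: reproduce the stated 125.** Take the group-by-time test of a repeated measures MANOVA (Pillai F approximation). Five assessments give 4 time contrasts; three groups give 2 group contrasts; s = 2.

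- df1 = 4 x 2 = 8
- df2 = 2 x (N - 3 - 4 + 2), which is 240 at N = 125
- noncentrality = f² x N x s = 0.0625 x 125 x 2 = 15.625
- power = 0.803 at N = 125 and 0.7995 at N = 124

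The smallest N that reaches 80% is 125, the stated figure, and no correlation is needed to obtain it. A one-way ANOVA gives 158. A between-groups main effect over five measures depends on rho (121 at 0.7, 127 at 0.75). The sample size therefore fits an analysis in which baseline is one of five repeated outcomes.

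**Step 2: compare the two ways of using baseline at one follow-up visit.** Assume a common variance σ², a common slope across arms, and correlation rho between baseline and follow-up.

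- Change from baseline: σ² + σ² - 2·rho·σ² = 2σ²(1 - rho)
- Adjusted for baseline: σ²(1 - rho²)
- Ratio, adjusted to change: (1 - rho²) / [2(1 - rho)] = (1 + rho)/2
- Saving: 1 - (1 + rho)/2 = (1 - rho)/2

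**Step 3: put in values.** The last column is the number of completers that a change-from-baseline contrast would need to match 120 completers (150 x 0.8) with adjustment: 120 / (1 - saving).

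| rho (assumed) | Saving, one visit | Equivalent of 120 completers |
|---|---|---|
| 0.3 | 35% | 120/0.65 = 185 |
| 0.5 | 25% | 120/0.75 = 160 |
| 0.7 | 15% | 120/0.85 = 141 |
| 0.9 | 5% | 120/0.95 = 126 |

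**Step 4: mean of the four post-baseline visits**, with equal correlations throughout.

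- Change: σ²[(1 + 3rho)/4 + 1 - 2rho] = 5σ²(1 - rho)/4
- Adjusted: σ²[(1 + 3rho)/4 - rho²] = σ²(1 - rho)(1 + 4rho)/4
- Ratio: (1 + 4rho)/5, so the saving is 4(1 - rho)/5: 56% at rho 0.3, 40% at 0.5, 24% at 0.7 and 8% at 0.9

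These savings apply to arm contrasts. They do not transfer one for one to the 8-df joint test, where the gain depends on how the effect is spread over the visits.

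**The case against.** The strongest objection is that the article does not exclude baseline adjustment. It commits to hierarchical linear models, leaves their handling of baseline open, and a full analysis plan may settle it. This stands in part. A hierarchical model with baseline as a covariate or with equal baseline means would recover most or all of the loss. But the article does state a model, its covariate and the number of repeated measures for the MANOVA, and that is the analysis the sample size matches. For that analysis the choice is made.

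Second, change from baseline is valid under randomisation and mirrors hypotheses worded as reductions. That also stands. A reader might infer that the planned test is biased, and nothing in the documents supports this. A baseline-adjusted contrast estimates the same difference in reduction, so the hypotheses need no rewording.

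Third, the trial was sized for an analysis with baseline as a repeated measure, so the stated 80% does not depend on adjustment. This is correct. The power of about 0.78 at 120 completers comes from the drop-out allowance (125 x 1.2 = 150, where 125/0.8 gives 157), which is a separate matter.

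Fourth, baseline adjustment is not better under every condition. The formula assumes equal variances and a common slope. Hypothesis 1 compares two arms with one, and with unequal allocation and arm-specific slopes a single-slope adjustment has no such guarantee.

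**Conclusion.** The point holds as one of precision. The stated MANOVA tests change from baseline with age as the only named covariate. Adjusting for baseline would reduce the variance of a single-visit contrast by (1 - rho)/2, which is 35% to 5% for rho from 0.3 to 0.9, given equal variances and a common slope. At high correlations the gain is small.

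Three stronger readings are tempting but unsupported:

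- **A fixed loss of 15 to 25%.** That range follows only if rho lies between 0.5 and 0.7, and no correlation is reported.
- **A power of 65% for the planned test.** That figure is for a single-visit two-sample t test with 80 v 40 completers, rho 0.5 and a difference of 0.46 SD; adjustment would raise it to about 78%. The 0.46 SD is not in the documents. It follows from f = .25 only if the three arm means are equally spaced (.25 x √6 x .75 = .459). If the two My Road Ahead arms have equal means, the difference is .25 x 3/√2 = 0.53 SD and the change-score power is about 78%. Neither is the power of the 8-df test.
- **Dilution of the effect by one fifth because baseline is averaged in.** This concerns a between-groups main effect over five visits. The hypotheses concern change over time, so it has little bearing on them.

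**What to change.** In the hierarchical (mixed) model already planned for the primary outcome, state one of two equivalent approaches:

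- the post-randomisation DASS-21 totals are the outcomes, with baseline DASS-21 total, its interaction with visit, and age as covariates; or
- all five assessments are outcomes, with baseline means constrained to be equal across arms, and age as a covariate.

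Test the hypotheses as arm contrasts at the post-intervention, 3 month and 6 month visits. Treat each secondary scale in the same way with its own baseline. If any precision gain is quoted, give the assumed correlation and a range.

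The cost is analysis wording and a few degrees of freedom, negligible at about 120 completers. No extra participants or questionnaires are needed. The wording should be settled before outcome data are analysed.
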